## Objectives

2

This study aims to evaluate the effectiveness of the MIG program for children and adolescents with ASD in improving fundamental motor skills (capacity) and in achieving functional goals, compared with conventional treatments (psychology based on cognitive and behavioral techniques and Applied Behavior Analysis, and motor physiotherapy). As a secondary objective, this study seeks to verify the effectiveness of the MIG program on balance, sociocommunicative skills, and motor skills (performance).

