### Sample size

3.5

The sample size was set at 66 participants, distributed into three groups with 22 individuals in each group. Sample size determination was based on the findings of a previous investigation that analyzed the effects of the MIG program in children with ASD (10). The calculation considered an effect size of 0.87, derived from outcomes of the Canadian Occupational Performance Measure, a statistical power of 80%, a significance level of *α* = 5%, and an estimated attrition rate of 20% over time. The calculation was performed using G*Power software version 3.1 (24).

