#### Conventional psychology

3.7.2

Participants in this group will receive intervention delivered by psychology professionals, based on cognitive and behavioral techniques and Applied Behavior Analysis, characterizing conventional psychological treatment. The intervention will be delivered over five weeks, with 50-minute sessions twice per week, totaling 10 sessions. The protocol will focus on the development of emotional regulation skills, including recognition of basic emotions (happiness, sadness, fear, disgust, anger, and anxiety) and their expressions, identification of emotions in oneself and in others, as well as strategies for appropriate emotional expression and regulation. Sessions will follow a structured therapeutic script, with clinical flexibility according to individual needs, without direct approaches to motor training or motor functional goal attainment. Interventions will be conducted in standard treatment rooms at the Reabilitar Clinic, in Ribeirão das Neves, Minas Gerais, Brazil.

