### Data analysis

3.10

Analyses will be performed using IBM SPSS Statistics software. Descriptive analyses will initially be used to characterize the sample in terms of age, sex, and level of support. Data distribution will be assessed using the Shapiro–Wilk test. Baseline group comparisons will be conducted using one-way analysis of variance (ANOVA) or Kruskal–Wallis tests, as appropriate. All analyses will follow the intention-to-treat principle. Linear mixed-effects models will be used to evaluate intervention effects over time, including group-by-time interaction terms. In the presence of significant interactions, *post hoc* analyses with Bonferroni correction will be performed. Missing data will be handled using maximum likelihood estimation within the mixed-effects models. A two-sided significance level of 5% (*p* < 0.05) will be adopted for all analyses.

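### Group comparisons wait on a three-arm interaction test that the psychology arm alone can trigger, and the Bonferroni step that follows lowers power for MIG versus physiotherapy with no allowance in the sample size

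*Protocol article*

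**What the plan says.** - **Data analysis (3.10):** "Linear mixed-effects models will be used to evaluate intervention effects over time, including group-by-time interaction terms". Post hoc analyses with Bonferroni correction follow "In the presence of significant interactions". Every analysis uses two-sided 5%. The section does not name a decisive contrast or visit, and it does not say how many comparisons Bonferroni covers.
- **Objectives (2):** MIG is to be assessed "compared with conventional treatments", namely psychology and motor physiotherapy. Neither is ranked above the other.
- **Conventional psychology (3.7.2):** this arm is delivered "without direct approaches to motor training or motor functional goal attainment".
- **Primary outcomes (3.8.1):** there are two, TGMD-2 for motor skills and COPM for functional goals.
- **Sample size (3.5):** participants are "distributed into three groups with 22 individuals in each group". "The calculation considered an effect size of 0.87", taken from COPM results, with 80% power, alpha 5% and 20% attrition. The section mentions neither an interaction test nor a multiplicity correction.

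**The concern.** The protocol gives one route to any statement about two groups. A non-directional test across all arms and visits must first be significant, and the pairwise tests then pay a Bonferroni penalty.

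This fits the question poorly in two ways. First, the interaction mixes psychology versus physiotherapy, and the three-month visit, with the contrasts that matter. On TGMD-2 any arm that trains movement may separate from one that does not, so the interaction can be significant when MIG and physiotherapy are equal. Second, the comparison that shows whether MIG adds to ordinary motor treatment has to pass both hurdles in a trial whose sample size appears to assume a single test.

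At stake are what a significant interaction, or a win over psychology only, will be taken to mean, and the chance of detecting a real advantage over physiotherapy.

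**Working it through.** **Inputs from the protocol.** Three arms of 22; three visits; effect size 0.87; 80% power; two-sided 5%; 20% attrition, so 22 × 0.8 = 17.6, about 18 completers per arm.

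**Assumptions, not in the protocol.** 0.87 is a between-group d in outcome SDs. The correlation between visits is 0.5 unless stated, so the SD of change, √(2(1 − 0.5)) = 1, equals the outcome SD. Data are complete at 22 or 18 per arm, the effect is equal at both follow-ups, and Bonferroni covers three pairs at one visit.

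**1. The plan's own figure.** A two-sided t-test at d = 0.87 needs 22 per arm for 80% power before attrition. Dividing by 0.8 gives 27.5, so 28 per arm or 84 in all (81 by the normal approximation). The stated 66 is reached by a two-sided test with no attrition allowance, or by a one-sided normal approximation with one (17 / 0.8 = 21.25, so 22). Neither route contains a 4-df test or a Bonferroni step.

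**2. The gate.** df = (3 − 1)(3 − 1) = 4 with time categorical.

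**3. How often the gate opens when MIG equals physiotherapy** (simulation; both arms above psychology by e):

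| e | Correlation | Interaction significant, 18 to 22 per arm |
|---|---|---|
| 0.87 SD | 0.5 | about 77–87% |
| 0.5 SD | 0.5 to 0.7 | about 30–58% |
| 0.3 SD of change | 0.5 to 0.7 | 10–15% (includes a three-month effect of half the size) |

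At e = 0.87, the gate followed by a Bonferroni-corrected win of MIG over psychology occurs in 45–53% of trials with 18 per arm and 59–65% with 22. A win of MIG over physiotherapy, false in this scenario, occurs in under about 1%.

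**4. Power for MIG versus physiotherapy when MIG is 0.87 above both comparators.** The noncentrality is d√(n/2): 0.87 × √11 = 2.89 at 22 per arm and 0.87 × √9 = 2.61 at 18. Bonferroni for three pairs uses 0.05 / 3 = 0.0167.

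| Rule | 22 per arm | 18 per arm |
|---|---|---|
| One contrast at 5% | 81–82% | 72–73% |
| One contrast at 0.0167, no gate | about 66% | about 55% |
| Gate, then 0.0167 | 60–65% | 45–54% |

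The range in the last row reflects whether the post hoc test compares means at the post-intervention visit (lower end) or changes from baseline (upper end); the protocol does not say which. Bonferroni costs about 15 points at 22 per arm (81 − 66) and about 17 at 18 (72 − 55). The gate takes a further 1 to 6 points (66 − 65, 66 − 60) and 1 to 10 points (55 − 54, 55 − 45) respectively.

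**The case against.** Several points on the other side are sound.

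- **The corrected pairwise test still protects the conclusion.** If MIG equals physiotherapy and both beat psychology, a significant interaction correctly rejects the hypothesis of no differences. A reader might infer that the plan invites false claims of MIG over physiotherapy. It does not: that error stays under about 1%. What remains open is which pairwise result supports the claim in the Objectives.
- **The active-versus-psychology effect is unknown.** A reader might infer that the interaction is likely to be significant whenever MIG equals physiotherapy. That needs an effect near 0.87, and the protocol's 0.87 comes from an earlier study of MIG, not from physiotherapy against psychology.
- **The power loss can be exaggerated.** A reader might infer that power is roughly halved, by setting about 46% under the planned rule against 83–84% for one baseline-adjusted contrast at 18 per arm. About 11 of those points (84 − 73) come from baseline adjustment, not from removing the gate or Bonferroni. Halving like for like needs about nine comparisons with 18 per arm (38–41%), or a smaller true effect (at d = 0.5 with 22 per arm, 37% falls to 17–21%).
- **Psychology is a stated comparator**, and COPM goals are chosen by parents and not limited to movement. Treating psychology as an attention control is clear for TGMD-2 and less so for COPM.
- **An analysis plan may name the contrasts.** That is fair as to what is absent. But the gate and the correction are stated as the rule, and the sample size is stated without them.

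**Conclusion.** The point holds in a limited form. The stated rule makes every group comparison depend on a test that cannot by itself answer whether MIG adds to physiotherapy, and it gives that comparison less power than the sample size section claims. At the planned effect, power falls by about 17 to 22 points with 22 per arm and by about 18 to 28 points with 18 per arm, mainly through Bonferroni.

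These figures rest on reading 0.87 as a between-group d, a correlation of 0.5 and three comparisons; a larger Bonferroni family would cost more. The frequency of an interaction driven by psychology alone is only a range, because the protocol gives no effect for it. The protocol supports neither a claim that power is halved at the planned effect nor a claim that the rule produces false superiority over physiotherapy.

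**What to change.** In Data analysis:

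1. Remove the requirement for a significant interaction.
2. For each primary outcome, pre-specify 1-df contrasts from the mixed model immediately post-intervention: MIG versus conventional physiotherapy at two-sided 5% and, if that succeeds, MIG versus psychology at two-sided 5%. The fixed order makes Bonferroni between these two unnecessary.
3. Claim superiority "compared with conventional treatments" only if both succeed. Report a win over psychology alone as exactly that.
4. Make the three-month contrasts and psychology versus physiotherapy secondary.
5. State how TGMD-2 and COPM share the 5%.

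If the Bonferroni post hocs are kept, restate the power in Sample size for that rule, with the number of comparisons and the expected completers.

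The cost is wording: the same model and no extra participants. With one contrast at 5%, power for MIG versus physiotherapy on one outcome returns to 81–82% at 22 per arm. With 18 completers it is still only 72–73%, and splitting the 5% between outcomes would lower both figures. Placing physiotherapy first is a choice the Objectives do not make, so the sponsor has to adopt it openly. The downside is that a significant interaction, or a win over psychology alone, no longer supports the headline claim.

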**Methods and analysis:**

This is a three-arm randomized controlled trial with concealed allocation and blinded outcome assessors. Sixty-six children with ASD, aged 6 to 12 years, classified as requiring level 1 or 2 support, will be randomized into one of three groups: (I) MIG program, (II) conventional psychological intervention, and (III) conventional motor physiotherapy. Interventions will last five weeks. Assessments will be conducted at baseline, immediately post-intervention, and three months after completion. Primary outcomes include fundamental motor skills and functional goal attainment. Secondary outcomes include measures of balance, sociocommunicative skills, and motor performance. Data will be analyzed using linear mixed-effects models, following the intention-to-treat principle.

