#### Primary outcomes

3.8.1

The Test of Gross Motor Development–Second Edition (TGMD-2) will be used to assess fundamental motor skills (25, 26). This standardized instrument quantitatively and qualitatively evaluates 12 motor skills, subdivided into locomotor and object control skills. Scores are derived from the sum of raw scores converted into motor quotients, allowing for normative performance analysis. Its validity and reliability for the Brazilian population with typical development were established by Valentini et al. (27), with subsequent application in studies involving children with ASD (28).

The Canadian Occupational Performance Measure (COPM) will be used to assess functional goal attainment (29). This semi-structured interview allows parents to identify, describe, and prioritize treatment goals relevant to their child's occupational performance. Each goal is rated on a 10-point scale for importance, performance, and satisfaction. The instrument demonstrates validity, reliability, and sensitivity to clinical change (29, 30).

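### Two primary outcomes are each tested at 5% with no rule linking them, so the chance of a false-positive primary interaction is up to about 9.75% if either outcome may count as success

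*Protocol article*

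**What the plan says.** The abstract of the Protocol article states: "Primary outcomes include fundamental motor skills and functional goal attainment". Section 3.8.1 assigns an instrument to each: "The Test of Gross Motor Development–Second Edition (TGMD-2) will be used to assess fundamental motor skills" and "The Canadian Occupational Performance Measure (COPM) will be used to assess functional goal attainment". Of the COPM it adds: "Each goal is rated on a 10-point scale for importance, performance, and satisfaction". It does not say which of these ratings is the primary variable.

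Section 3.10 gives the test: "Linear mixed-effects models will be used to evaluate intervention effects over time, including group-by-time interaction terms". When an interaction is significant, post hoc "analyses with Bonferroni correction will be performed". The level is "A two-sided significance level of 5" per cent, and it "will be adopted for all analyses".

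The objectives (section 2) name both outcomes as targets of the MIG program. They do not say whether one or both must improve for the program to be judged effective. Section 3.5 sizes the trial on an effect of 0.87 taken from the COPM, with 80% power, alpha of 5% and 20% attrition, giving 22 per arm.

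**The concern.** Each primary outcome gets its own interaction test at the full 5%. The Bonferroni correction comes later and works within one outcome's model, so it does not reach across TGMD-2 and COPM. No order of testing, split of alpha or success rule is given.

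This goes beyond a detail left to an analysis plan. Section 3.10 positively fixes the level for all analyses and says where correction applies. A later plan that split alpha or imposed an order would have to depart from that text.

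The protocol describes MIG as not yet evaluated in a randomized trial, and its discussion expects the findings to inform service planning. A mixed result, with one primary outcome positive and the other null, is quite possible. The plan cannot say whether that would count as effectiveness, so the choice could be made after the data are seen.

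**Working it through.** **Inputs.** Two primary outcomes (abstract, 3.8.1); 5% two-sided per analysis (3.10); three arms by three time points, so (3 − 1) × (3 − 1) = 4 degrees of freedom per interaction test; effect 0.87, 80% power, 20% attrition, 22 per arm (3.5). The correlation between the outcomes is not given, so a range of 0 to 0.9 is assumed.

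**The plan's own figure.** A two-sided two-sample t-test at 5% with effect 0.87 and 80% power needs 21.74, rounded up to 22 per arm. That is the number before any allowance for attrition, which is a separate matter. Power with 22 per arm is 0.805. With 22 × 0.8 = 17.6 per arm it is 0.707.

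**If either outcome suffices.** For independent tests the chance of at least one false-positive interaction is 1 − 0.95² = 0.0975. Whatever the correlation, it cannot exceed 0.05 + 0.05 = 0.10. Simulated pairs of correlated 4-df tests give:

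| Correlation | At least one false-positive interaction |
|---|---|
| 0 | 9.75% (exact) |
| 0.5 | 9.2% |
| 0.7 | 8.5% |
| 0.9 | 7.2% |

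**After the post hoc step.** A significant interaction is not yet a claim about MIG, because it may come from a difference between the two comparators. Both steps were therefore simulated with no true differences. The assumptions were change-from-baseline contrasts, a normal approximation, Bonferroni over the three pairs of arms, and a between-time correlation of 0.5 or 0.7. A false difference between MIG and at least one comparator, in either direction, occurred in about 3.0% of trials for one outcome and about 5.9% for two independent outcomes. In the direction favouring MIG, the two-outcome rate was about 3.0%, falling to about 2.6% at outcome correlation 0.7. With Bonferroni over six contrasts it was about 2.2% at correlation 0.

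**If both outcomes are required.** The chance that both interactions are falsely significant runs from about 0.25% (correlation 0) to 2.8% (correlation 0.9), so alpha is not inflated. The protocol gives no effect size for TGMD-2. If it were also 0.87, joint power with 22 per arm would be 0.805² = 0.65 for independent outcomes, rising towards 0.80 as the correlation approaches 1.

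**Effect of a correction.** Testing each outcome at 2.5% gives 1 − 0.975² = 4.94% for independent outcomes, and never more than 5%.

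**The case against.** Four arguments deserve weight.

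- **The inflation is conditional.** It arises only if a win on either outcome counts. The objectives join the outcomes with a plain conjunction, which could mean that both are required. This stands: 9.75% is an upper figure under one reading. But an objective is not a decision rule, and nothing excludes the either-outcome reading.
- **The interaction rate is not the rate of false MIG claims.** A reader might infer that false claims of MIG effectiveness nearly double from 5% to 10%. The documents do not support that, because the corrected post hoc step intervenes and the MIG-specific rate is about 6% two-sided. What remains is that this is about twice the rate with one outcome, and the correction does nothing across outcomes.
- **The stated 5% and 80% are not false in themselves.** A reader might conclude that one of them must be wrong on either reading. The text presents 5% as the level for each analysis, not for the whole trial, and never presents 80% as joint power. The fault is that neither figure describes the primary conclusion.
- **COPM might add a further test.** Counting performance and satisfaction separately would give 1 − 0.95³ = 14.3% for three independent tests. Section 3.8.1 only describes how goals are rated and does not say that the scores are tested separately, so this figure should not be relied on.

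It is also fair that motor capacity and parent-rated goals are distinct constructs that can be reported separately. That is a reason to write down a rule, and it bears on severity.

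**Conclusion.** The point holds in a conditional form. The protocol fixes 5% for each of two primary outcomes and has no control across them. If either outcome suffices, the chance of a false-positive primary interaction is 9.75% for independent outcomes and about 7% at correlation 0.9. False MIG-specific claims reach about 6% two-sided under the assumptions listed, roughly double the one-outcome rate. If both are required, error is controlled, but power for the joint conclusion was never computed; it is about 65% for independent outcomes, equal effects of 0.87 and no attrition. The correlation and the TGMD-2 effect are assumptions. This should be fixed, but it does not show that the trial's stated figures are wrong.

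**What to change.** Add one paragraph to section 3.10 that adopts one of two rules and says that effectiveness may be claimed only under it:

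- **Holm** across the two primary interaction tests at an overall two-sided 5%: the smaller p-value is tested at 2.5% and, if that is significant, the other at 5%.
- **Fixed sequence** starting with COPM, the outcome the trial was sized on: TGMD-2 is tested at 5% only if COPM is significant at 5%. The reverse order would put the only outcome with a power basis behind one that has none.

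Under either rule, name one COPM score as the primary variable. The post hoc Bonferroni within each outcome can stay.

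**Cost.** Under Holm, pairwise t-test power at the 2.5% step is about 71% with 22 per arm, against 80% at 5%; with 17.6 per arm it is about 60%, against 71%. Keeping 80% at 2.5% would need 27 per arm before attrition and 27 / 0.8 = 33.75, so 34 per arm (102 in total), after it. Under the fixed sequence the first test loses no power, but TGMD-2 cannot support a confirmatory claim if COPM fails. If the sponsor intends that both must succeed, section 3.10 should say so; alpha then needs no change, but section 3.5 should report joint power with a stated TGMD-2 effect.

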## Ethics and dissemination

4

Ethical approval was obtained from the Research Ethics Committee of the Faculty of Medical Sciences of Minas Gerais, Brazil (Approval No. 7,456,658). The trial was prospectively registered in the Brazilian Registry of Clinical Trials (RBR-7r6n8zd) and the WHO Universal Trial Number system (UTN: U1111-1326-2272). Written informed consent will be obtained from parents or legal guardians, and assent will be sought from participating children when developmentally appropriate, prior to any study procedures. All procedures will comply with national and international ethical standards for research involving human participants. Adverse events will be monitored and recorded throughout the intervention period, and appropriate clinical referral will be provided if necessary. Results will be disseminated through peer-reviewed publications, scientific conferences, and reports to participating families and partner institutions.

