Despite growing evidence indicating that motor impairments are highly prevalent in ASD and influence sociocommunicative development, a significant gap remains in clinical practice, which the MIG protocol seeks to address. The effects of MIG have been investigated in children and adolescents with ASD and indicate that the intervention promotes meaningful functional improvements when assessed through parent-reported outcomes and measures sensitive to change (10, 11, 22). *Although no previous feasibility studies have been conducted, pre- and post-intervention studies indicate that children and their families are able to attend and complete most of the sessions required by this intensive program, suggesting good feasibility and adherence* (10, 11, 22)*.* Taken together, these studies suggest that MIG is a promising intervention capable of producing functional, communicative, and motor improvements, with strong family acceptance and alignment with contemporary family-centered care guidelines. However, MIG has not yet been evaluated in randomized controlled trials. Therefore, it is necessary to conduct a study that evaluates the potential effects of MIG when compared with conventional interventions.

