### Design

3.1

This study is a three-arm, single-blind randomized controlled trial designed to compare the Global Integration Method (MIG) program with conventional physiotherapy and conventional psychological interventions. Participants will be randomly allocated to one of three groups, with concealed allocation and blinded outcome assessors. Assessments will be conducted at three time points: baseline, immediately after the intervention period, and three months after intervention completion. The trial protocol was developed in accordance with the Standard Protocol Items: Recommendations for Interventional Trials (SPIRIT) guidelines (23).

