#### MIG program

3.7.1

Participants in this group will receive a protocol specifically structured to assess the motor component of the MIG program. The intervention will be delivered by physiotherapists with prior experience in MIG and additional training provided by an interdisciplinary team (psychologists, speech-language pathologists, and occupational therapists), ensuring standardization of the research protocol implementation. The motor component will be delivered in three weekly sessions, each lasting 50 min, over a period of five weeks, following a previously defined structure. *Although the MIG is conceived as an intensive interdisciplinary program, the present trial was designed to isolate and evaluate only its motor component; therefore, the dosage reported here refers exclusively to the physical therapy sessions and does not correspond to the total interdisciplinary workload of the complete MIG protocol.*

In all sessions of the motor component protocol of the MIG program, the child will wear the MIG Flex therapeutic suit. This suit provides proprioceptive input and postural support during motor activities. This resource serves a dual function by promoting bodily stability and improved motor organization, while reducing the cognitive load required for postural maintenance and movement coordination, thereby freeing attentional and cognitive resources that can be directed toward interaction, play, and communication. At the beginning of each session, the physiotherapist will place and adjust the MIG Flex on the child and then initiate the narrative designed for that session. The narrative will introduce the main character, the setting, and the temporal context (initial situation), as well as the problem, triggering event, or central challenge (initiating event). The character's feelings or emotions and the plan for problem resolution will also be explicitly presented; this plan will correspond directly to the motor activities the child must perform to “help” the character, together with psychoeducational components about emotions aimed at promoting generalization of concepts and strengthening cognitive flexibility by allowing the participant to recognize common principles across different symbolic situations. The narratives used in sessions 01 and 15 are described in Supplementary Material 1.

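### The stated adverse-event window ends with the five-week intervention, so delayed, persisting or late-reported events before the three-month assessment fall outside it

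*Protocol article*

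**What the plan says.** Harms appear in one sentence of the protocol article, in section 4 (Ethics and dissemination): "Adverse events will be monitored and recorded throughout the intervention period", followed by a provision for clinical referral where needed. No other section mentions adverse events, and none gives a later end to the recording window or a reason for ending it there.

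The length of the window follows from the treatment schedule. The abstract says "Interventions will last five weeks". Section 3.7.1 gives the MIG schedule as "three weekly sessions, each lasting 50 min, over a period of five weeks", and sections 3.7.2 and 3.7.3 give the two comparators the same five weeks.

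Section 3.1 sets the assessments at "baseline, immediately after the intervention period, and three months after intervention completion", and section 3.9 repeats the three time points. In section 3.9 the COPM, DCDQ and VABS are all obtained by interviewing parents, so a parent is already in contact with the study at both post-baseline visits.

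On prior evidence, the Introduction states: "However, MIG has not yet been evaluated in randomized controlled trials".

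**The concern.** The trial looks for benefit up to three months after treatment ends but, as written, looks for harm only while treatment is being given. Section 4 ties recording to a named period, so the point concerns a stated window and not merely a detail left unsaid.

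The events at stake are those that begin after the last session, those that began earlier and have not resolved, and those that a parent first mentions at the later visit. Under the stated rule none of these has to be recorded in any arm.

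The gap matters somewhat more here because this would be the first randomised comparison of MIG. The Introduction describes the earlier pre-post studies in terms of function, attendance and family acceptance, and reports no safety result from them. The MIG arm trains in a therapeutic suit (section 3.7.1), and Table 1 includes jumping, single-leg and unstable-surface tasks. The Discussion expects the results to inform clinical decisions and service planning, and a fuller harms record would serve both uses.

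**Working it through.** The article gives no figure for adverse-event coverage, so there is no stated number to reproduce. The check compares the recording window with time on study.

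**Inputs**
- Recording window: the intervention period (section 4).
- Intervention length: 5 weeks in each arm (abstract; sections 3.7.1 to 3.7.3).
- Last assessment: three months after the intervention ends (sections 3.1 and 3.9). *Assumption:* three months is 12 to 13 weeks.
- Sample size: "The sample size was set at 66 participants, distributed into three groups with 22 individuals in each group" (section 3.5).
- Attrition: 20% over time (section 3.5). *Assumption for the sensitivity check:* all of it occurs at week 5, the end of the intervention.

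**Calendar time per child**

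Share covered = intervention weeks / (intervention weeks + follow-up weeks).

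| Three months taken as | Covered | Not covered |
|---|---|---|
| 12 weeks | 5/17 = 29.4% | 12/17 = 70.6% |
| 13 weeks | 5/18 = 27.8% | 13/18 = 72.2% |

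**Person-weeks, 66 children, 13 weeks of follow-up**
- No loss: 66 × 5 = 330 covered; 66 × 13 = 858 not covered; total 1,188. Covered: 330/1,188 = 27.8%.
- 20% lost at week 5: follow-up is 66 × 0.8 × 13 = 686.4; total 330 + 686.4 = 1,016.4. Covered: 330/1,016.4 = 32.5%; not covered: 67.5%.

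Under each assumption, about two thirds or more of the time on study lies outside the window.

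**What lies inside the window**

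All sessions in all three arms take place within the five weeks. Section 3.7.1 has the suit worn in the MIG sessions, and no use at home is described. The home task in section 3.7.1 reinforces the story content and is not described as motor training. So all described exposure falls inside the window, and the uncovered 12 to 13 weeks contain no study treatment. The percentages therefore measure follow-up time without harms recording, not exposure without it.

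**The case against.** The strongest case against the point has four parts.

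*The exposure is covered.* This stands. A reader might infer from the 70% or so of uncovered time that most of the risk goes unobserved. The documents do not support that, since every described session and all described suit use fall inside the window. The loss is confined to delayed, persisting or late-reported events.

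*The text does not forbid later recording.* This stands in part. Section 4 names a period without expressly excluding anything after it, and a journal article is a condensed document. The plain reading is still that recording runs for that period, and nothing in the article extends it.

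*Safety is not an objective or an outcome.* This is correct: sections 2 and 3.8 list neither, and no section plans a conclusion that MIG is safe. Harms data would be a by-product of the trial, which limits the weight of the point.

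*Asking parents about harms could unblind assessors.* This stands and shapes the fix. Section 3.6 says participants cannot be blinded, and section 3.9 has blinded assessors interview parents, including for the COPM, a primary outcome. A parent's answer about the suit could reveal the arm.

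A reader might also infer that the record is biased between arms because MIG has 3 × 5 = 15 sessions and each comparator 2 × 5 = 10. The documents do not support this. The window is the same five calendar weeks in each arm, and the article does not say that events are noticed only at sessions. If more sessions do cause more events, the higher count correctly describes the programme as delivered.

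**Conclusion.** The point holds in a limited form. On its plain reading, section 4 leaves 12 to 13 of 17 to 18 weeks on study without harms recording, although all children are due for assessment at the end of that time. What can be missed is delayed, persisting or late-reported events in any arm; events during treatment are within the window.

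The weight is minor to moderate. This rests on three things: reading section 4 as setting the end of recording, taking three months as 12 to 13 weeks, and the absence of any text that extends the window. The primary efficacy comparisons, sample size and randomisation are not affected. The change is worth making because it improves harms capture at a visit already planned, for an intervention with no earlier randomised trial.

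**What to change.** In section 4, extend adverse-event recording in all three arms to the three-month assessment. Put one identical structured question to parents at the post-intervention and three-month visits.

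To protect blinding, collect the answer on a parent-completed form or through existing study staff who are not blinded assessors, and only after outcome scoring for that visit is complete. Keep the answers from the assessors.

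Report the events per child by arm, separately for the intervention and follow-up periods, so that events arising under treatment can be told apart from later ones.

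The cost is a few minutes at two scheduled visits and one item on the case report form. There are two small downsides: more unrelated minor events will be listed, and the study team must take care that the answers do not reach the assessors. If the sponsor prefers to end recording with the intervention, section 4 should say so expressly and give the reason.
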